#### Sexual Agreements

All surveys include questions taken from previous studies of male couples’ sexual agreements [45]. Participants are asked which of the following best describes their current sexual agreement with their main partner: “neither of us can have sex with outside partners,” “we can have sex with outside partners, without any conditions or restrictions,” “we can have sex with outside partners, but with conditions or restrictions,” or “we do not have an agreement.” Additional items about agreements will further assess whether couples permit (or do not permit) that certain sexual behaviors, mainly CAI and oral sex, can occur with outside partners. In follow-up surveys, participants are asked whether their agreement had been broken in the previous 3 months, if they disclosed the agreement breakage to their partner, whether they have changed their agreement, and, if relevant, how their agreement had changed.

#### Sexual Risk-Taking

Behavioral measures adapted from the National HIV Behavioral Surveillance behavioral inventory, as well as from studies using behavioral measures among thousands of MSM [46,47], will collect information both on sexual behaviors with the main sex partner in the 3 months before the interview and on sexual behaviors with all sex partners outside the relationship that may exist. For sex with the main partner, men are asked to estimate the number of anal sex acts with the main partner and the number of those acts that were condom protected. For outside the relationship, men are asked a series of questions about each outside partner. Questions include HIV status of that partner (if known), whether the sex outside the relationship was disclosed to the main partner, the number and type of sex acts (ie, oral, anal, both, etc) with each outside partner, and the proportion of those sex acts that were protected by condoms. Data on use of and adherence to preexposure prophylaxis (PrEP) are collected.

#### Linkage to HIV Care

The following outcomes as indicators of linkage to care, per the recent recommendations of the Institute of Medicine [48], are measured within 3 months of HIV diagnosis via self-report [49,50]: (1) attending at least one clinical care appointment, (2) having at least one CD4 test performed, and (3) having at least one viral load test performed.

### Secondary Outcomes: Dyadic Characteristics

#### Overview

The four elements of Lewis’ model [44]—Predisposing factors of couple, Partner’s transformation of motivation, Process of communal coping, and Use of communal coping—are referred to as dyadic characteristics. In a recent RCT of CHTC, scales were developed to capture these constructs; all scales showed strong reliability and evidence for construct validity was obtained for all scales [51]. In this intervention, each of the scales is collected in the baseline and follow-up surveys.

#### Predisposing Factors of Couple

Several scales are used to measure this element. The Perceived Severity of HIV Scale involves the perception of the personal, psychosocial, and physical consequences of a particular health threat. A total of 13 items were developed that crossed the three pertinent consequences of a particular health threat: personal, psychosocial, and physical. The Preferences for General Lifestyle Outcomes Scale is defined as the degree to which interacting partners agree about the shared or joint outcomes in their relationship and is composed of two subscales: the Preferences for General Lifestyle Scale and the Preferences for Sexual Health Outcomes Scale. The Preferences for General Lifestyle Scale includes six outcomes, including diet, nutrition, and social activities. The Preferences for Sexual Health Outcomes Scale relates to sexual health, for example, reducing one’s risk for HIV. In addition, scales to measure other predisposing factors of couples are proposed for inclusion. Conflict style determines how respondents typically handle conflict in their relationships, so the Conflict Style Inventory will be included [52]. Communication style will be measured with the Communication Patterns Questionnaire Constructive Communication subscale [53]. Finally, problem-solving skills are measured with the Adherence Problem Solving/Readiness Scale [54].

#### Partner’s Transformation of Motivation

In a recent RCT of CHTC, two measures were developed: ability of the participants to respond (1) cognitively and (2) emotionally to the health threat [21]. The scale for emotional response includes whether the respondent reports being fearful, nervous, or anxious about HIV. The scale for cognitive response includes whether the respondent reports understanding the risks of HIV transmission associated with being in a serodiscordant relationship and the risks associated with outside sex partners.

#### Process and Use of Communal Coping

Several scales are also used to measure this element. The Outcome Efficacy to Reduce HIV Threat Scale discusses how communal coping involves couples working together and making decisions together to reduce the health threat. Three subscales were created to capture the full range of outcome efficacy related to these three processes of communal coping. For the first subscale, Joint Effort, the stem “My partner and I believe that ‘working together’ versus on our own is an effective strategy” is used. For the second subscale, Communication, the stem “Communicating with my partner is an effective strategy for...” is used. For the third subscale, Planning and Decision Making, the stem “My partner and I making decisions together rather than separately is an effective strategy” is used. The items for each of the three subscales were the same as the items used for the Preference for Sexual Health Outcomes Scale. The Couple Efficacy to Reduce HIV Threat Scale defines couple efficacy as a couple’s confidence that together they can engage in communal coping efforts.

In addition to the outcomes tied to Lewis’ framework [44], we also include two additional outcomes: violence and relationship dissolution. The Conflict Tactics Scale Revised [55] assesses both perpetration and experience of IPV. Relationship dissolution is assessed using an item that asks each partner in the couple to report the current status of their relationship and reason for dissolution at follow-ups.

### Statistical Analysis: Dyadic Characteristics

#### Overview

Dyadic characteristics will be analyzed within and between couples over time by HIV status and study arm (control vs experimental). Simple *t* tests and chi-square tests will be used to investigate systematic differences among average scales between experimental and control arms and between serodiscordant and seroconcordant-negative couples. Next, regression, generalized linear mixed models, and marginal models via generalized estimating equations (GEE) will be used to model longitudinal item and scale measures. In general, participants will be nested within couples, so the participant is regarded as the experimental unit; outcomes within couples and over time are potentially correlated. Initially, an unstructured serial correlation structure for the within-subject covariance and a single correlation parameter to describe the within-couple correlation will be assumed. If the unstructured covariance structure is too weak leading to nonconvergence issues and weak identification, more structure will be placed on the residuals and stronger models will be considered, such as an exchangeable or autoregressive correlation structure. Statistical inference will be likelihood based for the mixed models while generalized score and Wald tests will be used for statistical inference in the marginal models. In the presence of missing data, both mixed and marginal models accommodate missing data (eg, dropout), although the former under a weaker (missing at random) assumption.

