The CHTC session is conducted via video chat using VSee. Figure 3 is an example of the VSee interface that participants see when waiting for their prescheduled counseling session to begin. The session is conducted by a counselor who is trained in CHTC and will last approximately 30-45 minutes. Pretest counseling focuses on the couple’s relationship, their perceived HIV risk factors, and focuses on their sexual agreement. Both partners individually conduct their own HIV test and read their individual results together, as instructed by the counselor. Participants are asked to show the counselor their test result; the counselor then confirms the test result for accuracy of interpretation. Figure 4 is the interface the participant sees when entering their HIV testing result to the Nexus website. Posttest counseling focuses on dyadic prevention messages and revisits the couple’s HIV risk concerns and sexual agreements in light of their test results. The counselor records the couple’s HIV test results in the couple’s study file. The counselor is trained to keep focus on the couple in the event that an HIV-positive result is given during a CHTC session. While a focus on the immediate needs of the HIV-positive partner is required, the discussion remains focused on how the couple can work together to keep the positive partner healthy and to keep the risk of HIV within, and not outside of, the relationship with other partners, while also meeting the needs of both partners within the male couple. If both couples are seroconcordant negative, the counselor discusses strategies that will minimize the risk of HIV transmission within and/or outside the relationship. The prevention-counseling element of the CHTC session focuses on talking the couple through prevention options and asking them to consider which prevention options may work best based on their relationship needs, context, and unique risk profile.

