#### Sexual Risk-Taking

The definition of at-risk sex will be serostatus specific. For serodiscordant couples, at-risk sex will be CAI with either their main or outside partners. For seroconcordant-negative and seroconcordant-positive couples, at-risk sex will be CAI with outside sex partners. While data on PrEP use and adherence will be collected, the definition of at-risk sex focuses on condom use given the CDC recommendation for continued condom use for those adopting PrEP. The incidence of at-risk sex acts will be calculated as an incidence density, with the numerator being the number of individual at-risk sex acts and the denominator being person-years of follow-up time. Comparisons of the incidence of at-risk sex acts will be made by comparing incidence densities between the two arms. Incidence rates per couple-year of follow-up will be estimated and compared using exact methods based on the Poisson distribution by using the GEE approach. Baseline covariates include race, age, and duration of relationship. Period incidence rates—6-monthly incidence density rates—of at-risk sex will be estimated by performing a GEE Poisson regression analysis of the 6-monthly counts. This will be implemented using the PROC GENMOD procedure by SAS (SAS Institute Inc) [56] and using an exchangeable correlation structure for the repeated observations of couples. The incidence density ratio, or incidence rate ratio (IRR), is the ratio of the incidence density in one treatment group (intervention arm) to that of another group (control arm). Results by each baseline covariate will be summarized as the IRR and the 95% confidence interval. These analyses will be descriptive and include analyses stratified by race/ethnicity. Prevalence of each outcome will be calculated and prevalence of outcomes will be compared in the control and intervention groups using chi-square tests or Fisher’s exact tests, as appropriate.

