### Cost Analysis

To examine the cost of the proposed intervention, cost data are collected by input type and by activity, using an activity-based costing matrix. Input types include study personnel salaries and benefits, supplies, equipment, HIV testing kits, and training materials. Activities include training (ie, counselors and crisis counseling), recruitment of participants, VSee video-based chat, follow-up, and linkage to care. For the experimental arm, counselors record the time spent per session of the counselor because these are the only additional (ie, incremental) costs incurred relative to the control arm.

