### Sample Size

The goal is to enroll and maintain a sample of 400 male couples: 200 serodiscordant and 200 seroconcordant couples, 100 of each couple per arm (experimental vs control). To achieve this, the intervention aims to screen approximately 1000 male couples—500 serodiscordant and 500 seroconcordant male couples—and will exclude those with a recent (<12 months) history of IPV. Assuming 15% of male couples have a recent history of IPV, this will produce approximately 850 couples for randomization, 425 per arm. Allowing for 20% loss to follow-up and additional 20% relationship dissolution, this will produce a sample of 400 male couples who are expected to complete the prospective RCT. The sample size is calculated based on the detection of significant changes in each of the main outcomes (ie, changes in sexual risk-taking, such as CAI), formation and adherence to explicit sexual agreements, and relationship functioning for the management of HIV risk. As an example, we will assume that about 25% of male couples change agreement status after couples counseling and we will use a two-sample test of binomial proportions with type I error rate at 5%. Using these assumptions, it is determined that 52%, 67%, and 85% statistical power is necessary to detect a difference of 10%, 12%, and 15%, respectively, in a change-of-agreement status between the two arms within seroconcordant or serodiscordant groups (ie, comparing 150 male couples per arm). In other words, under the same conditions, the probability is .52, .67, and .85 that the lower bound of the confidence interval for the proportion change in agreement status in the intervention arm is at least 3%, 5%, and 8% different than the proportion in the control arm, respectively, when the alternative hypothesis is true. If data is pooled across seroconcordant and serodiscordant couples, assuming that combining data makes sense in terms of the magnitude and direction of the intervention effect, then 81%, 92%, and 99% statistical power is necessary to observe differences of 10%, 12%, and 15%, respectively (ie, comparing 300 male couples per arm). In this case, at least 80% statistical power will be necessary to detect as little as a 5% difference between the lower bound of the confidence interval for the proportion in the intervention versus the control arm. Based on discussions with participant advocates and partnered community-based organizations, it is projected that any difference exceeding 5% would be scientifically meaningful and would have public health impact. The analysis also considers differences in linkage to HIV care among HIV-positive individuals in each arm, but it is not powered to detect significant differences, given the small number of incident positive cases.

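### The counselor level, which exists only in the experimental arm's session, is missing from the stated correlation structure; if counselors differ, intervals for the arm effect on agreement, sexual-risk and dyadic-scale outcomes are too narrow

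*Protocol article*

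**What the plan says.** **Delivery.** The Intervention section says of the experimental arm: "The session is conducted by a counselor who is trained in CHTC and will last approximately 30-45 minutes". The Cost Analysis section shows that more than one person does this: "counselors record the time spent per session of the counselor". It does not say how many. The Introduction contrasts these couples with control couples, who self-test with no counselor present.

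**Analysis.**
- The Overview under Statistical Analysis: Dyadic Characteristics nests participants within couples, starts from an unstructured serial covariance within subject, and adds one parameter for the couple: "a single correlation parameter to describe the within-couple correlation will be assumed". If that model fails to converge, the stated fallback is a simpler serial structure. The t and chi-square tests named there have no cluster term.
- Under Sexual Risk-Taking, counts go into a GEE Poisson model "using an exchangeable correlation structure for the repeated observations of couples".
- Under Sexual Agreements, percentages are compared between arms, and an actor-partner model with the dyad as unit is used for predictors.

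Counselor does not appear anywhere as a cluster, random effect or covariate.

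**Power.** The worked example in Sample Size assumes that "about 25% of male couples change agreement status after couples counseling" and applies a plain two-sample test of proportions.

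**The concern.** Randomising couples to a session led by one of several counselors creates a partially nested design: a grouping level above the couple in one arm and none in the other. The session is tailored talk about the couple's agreement and prevention options, so it is plausible that counselors differ in how often their couples change an agreement. That is the outcome used in the power example, and a shift to safer agreements is named as a focus of the arm comparison.

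If counselors do differ, outcomes of couples who share one are correlated. Clustering the GEE on couples does not absorb this, because different couples are still treated as independent. Standard errors in the experimental arm are then too small for inference beyond the particular counselors, and a result carried by one counselor could be credited to the service in general. The Discussion looks toward expanding the service, so the wider inference is at least in view.

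The article does not simply leave the dependence structure open. It writes the structure out level by level and omits one that its own delivery creates.

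**Working it through.** **1. Do the plan's power figures contain a counselor effect?**

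The plan states that "52%, 67%, and 85% statistical power is necessary to detect a difference of 10%, 12%, and 15%, respectively" at 150 couples per arm, and "81%, 92%, and 99% statistical power is necessary to observe differences of 10%, 12%, and 15%, respectively" at 300 per arm. A two-sided 5% test with independent couples and the 25% variance in both arms has SD = √(0.25 × 0.75) = 0.433, SE = 0.433 × √(2/n), and power ≈ Φ(difference/SE − 1.96).

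| Couples per arm | SE | 10 points | 12 points | 15 points |
|---|---|---|---|---|
| 150 | 0.0500 | 51.6% | 67.0% | 85.1% |
| 300 | 0.0354 | 80.7% | 92.4% | 98.9% |

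These reproduce the stated figures, so the figures assume independent couples in both arms and include no counselor design effect.

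**2. What could the omission do to the error rate?**

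Inputs from the article:
- 200 couples per arm, from the enrolment goal of 100 per arm in each of two serostatus strata.
- 76.6% (85/111) of experimental couples completing the session, from Results.
- Nominal error 5%.

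Assumptions, because the article gives neither figure:
- Number of counselors k = 2, 4 or 8, with equal loads.
- Intraclass correlation (ICC) among attending couples of the same counselor = 0.01, 0.02 or 0.05.

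Formulas:
- Attending couples per counselor: m = 200 × 0.766/k = 153.2/k.
- Design effect in the experimental arm, with only attenders clustered: DE = 1 + 0.766 × (m − 1) × ICC.
- Variance of the arm difference relative to the independent case: V = (1 + DE)/2.
- Error of the unadjusted test, for a mean effect of zero across counselors: 2 × [1 − Φ(1.96/√V)].

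Example with k = 4 and ICC = 0.02: m = 38.3; DE = 1 + 0.766 × 37.3 × 0.02 = 1.57; V = 1.286; √V = 1.134; 1.96/1.134 = 1.73; error = 8.4%.

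| Counselors | m | ICC 0.01 | ICC 0.02 | ICC 0.05 |
|---|---|---|---|---|
| 2 | 76.6 | 8.4% | 11.9% | 21.0% |
| 4 | 38.3 | 6.7% | 8.4% | 13.4% |
| 8 | 19.15 | 5.8% | 6.6% | 9.1% |

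The standard error of the arm difference is understated by a factor √V, from 1.03 (k = 8, ICC 0.01) to 1.56 (k = 2, ICC 0.05).

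**3. Which outcomes does this reach?**

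| Outcome | Stated analysis | Counselor contact |
|---|---|---|
| Dyadic scales | Mixed models and GEE | Session in experimental arm only |
| Sexual risk | GEE Poisson, clustered on couples | Session in experimental arm only |
| Sexual agreements | Percentages by arm; actor-partner model | Session in experimental arm only |
| Linkage to care | Percentages by arm | Follow-up of test-positive participants in both arms (Intervention section) |

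The one-arm argument therefore applies to the first three rows and not to the last.

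**The case against.** Several counter-arguments have weight.

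- **Left to the analysis plan.** This is a condensed article, and the correlation structure is introduced as an initial assumption. A provider effect could sit in a fuller document. That lowers the grade of the point, but the levels are spelled out here and the only stated fallback is a simplification.
- **Type I error.** A reader might infer that the tests exceed 5% whatever the truth. The documents do not support that. Couples are randomised individually, and if the session changes nothing for any couple, counselors cannot create differences and the test keeps its size. Inflation needs counselor effects that really differ while averaging to zero, and a conclusion that goes beyond these counselors. Treating the counselors as fixed is legitimate, and the article does not say which target is meant.
- **Scope.** A reader might infer that every arm comparison is affected. Linkage to care is not, for the reason in the table. The article also labels its agreement and sexual-risk analyses descriptive, although both compare arms.
- **Size.** The number of counselors and the ICC are both assumed. Nothing in the article shows that the upper end is realistic for self-reports at 3 and 6 months after one session of 30 to 45 minutes.
- **Feasibility.** With two to four counselors the variance is barely estimable. Couples choose their own appointment, so counselor groups form after randomisation, and an estimated counselor variance may mix couple selection with counselor skill.
- **Model fit.** A random effect cannot simply be added to a marginal GEE Poisson model or to a comparison of percentages.

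These points limit the claim and shape the remedy. None of them supplies the missing level.

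**Conclusion.** The point stands in a limited form, as a worthwhile improvement and not as an error that invalidates the plan. More than one counselor delivers the session, in the experimental arm only, and the stated analyses allow correlation only within person and within couple. If counselors differ in effect and the conclusion is meant to extend past them, intervals for the arm effect on dyadic-scale, sexual-agreement and sexual-risk outcomes are too narrow.

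The true size is unknown. Under the assumptions above, a nominal 5% error becomes about 5.8% to 21%. The low end is negligible, and with many counselors or an ICC near zero little would remain.

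**What to change.** 1. Record the identifier of the counselor with each session. Counselors already log session time and test results, so this adds one field.
2. For the dyadic-scale mixed models, prespecify a sensitivity analysis with a counselor random effect in the experimental arm only and small-sample degrees of freedom. Keep couples who do not attend as singletons, so that all randomised couples stay in.
3. For the GEE Poisson sexual-risk analysis and the agreement comparison, keep the stated models and report the arm effect leaving out one counselor at a time.
4. If there are too few counselors to estimate the variance, use the leave-one-out results for all of these outcomes and limit the conclusion to these counselors.

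The cost is one stored identifier, a few extra analyses, and wider intervals if counselors do differ. Enrolment and delivery do not change.
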